### Procedure

#### Oncology staff engagement and consent

Oncology staff (including specialists and nurses) will be invited to participate via email and sent an introductory summary, information sheet and consent form. Treating clinicians are asked to provide permission for research staff to contact their patients, and consent to participate in an evaluation interview at study close. Consenting oncology staff will receive training resources and participate in orientation sessions on how to use the PROMPT-Care system in routine clinical practice at study start along with refresher resources and orientation throughout the trial as needed.

#### Patient identification and consent

Participating clinicians will review their clinic lists to identify eligible patients who have appointments scheduled within the coming two (2) months. Two patient recruitment approaches will be utilised to achieve a similar proportion of both patients in active treatment and those in follow-up care.

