### Control population

A list of potential control individuals (minimum *n* = 1408) will be extracted from hospital databases of the general cancer patient population who were seen at the participating cancer therapy centres during the study period.

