### Sample size

A minimum sample size of 1760 (352 intervention and 1408 control) patients is required to detect a 14% reduction in the number of ED presentations in the PROMPT-Care group compared with the control group. This is based on the assumed rate of ED presentations being 1.4 visits per patient during the study period, a 1:4 ratio of PROMPT-Care to control group patients, 80% power and 5% statistical significance.

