### Statistical analyses

Descriptive statistics will be generated for all socio-demographic and clinical characteristics, and outcome measures. A multivariable Poisson or negative binomial regression (depending on over-dispersion) will be used to determine whether the rates of ED presentations were different between the PROMPT-Care and control groups adjusting for covariates (such as age, sex, stage of disease, and treatment status). Number of referrals to allied health services will be analysed similarly. Multivariable Cox proportional hazards model will be used to analyse length of time from start to end of chemotherapy adjusting for covariates.

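### Intervention patients come only through consenting clinicians and controls from the whole centre population, so clinician differences could partly confound the ED and referral comparisons

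*Protocol article*

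**What the plan says.** **Intervention group.** Under Oncology staff engagement and consent, staff "will be invited to participate via email and sent an introductory summary, information sheet and consent form". The same section adds: "Treating clinicians are asked to provide permission for research staff to contact their patients". Under Patient identification and consent, "Participating clinicians will review their clinic lists to identify eligible patients who have appointments scheduled within the coming two (2) months". The In clinic and Mail-out sections describe how identified patients are approached; neither gives another source of patients.

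**Control group.** Under Control population, a list of potential controls (at least 1408) is to be "extracted from hospital databases of the general cancer patient population who were seen at the participating cancer therapy centres during the study period". The limit is by centre and period. No limit by clinician is stated.

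**Analysis.** Under Statistical analyses, "A multivariable Poisson or negative binomial regression (depending on over-dispersion) will be used" for ED presentations, "adjusting for covariates (such as age, sex, stage of disease, and treatment status"). Allied health referrals are analysed in the same way. Treating clinician, specialty, tumour site and centre are not named.

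**The concern.** An intervention patient must pass a gate that no control is said to pass: the treating clinician has to have joined, permitted contact and listed the patient. A patient of a clinician who declined cannot be in the intervention group but, on the plain reading, can be a control.

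Clinicians who volunteer for a supportive-care system may differ from those who do not in specialty, tumour stream and readiness to refer. The Discussion stresses that the trial spans many tumour types and both treatment and follow-up, so ED rates may well vary between practices. Referral to allied health is usually a decision of the care team, so that secondary outcome is the more directly exposed. A larger sample would not reduce this kind of bias.

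**Working it through.** **1. The plan's own figure.** Inputs from Sample size: control rate 1.4 visits per patient, 14% reduction (rate ratio 0.86, intervention rate 1.4 × 0.86 = 1.204), ratio 1:4, 80% power, 5% significance taken as two-sided. With a Poisson log rate ratio:

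n (intervention) = (1.960 + 0.842)² × [1/1.204 + 1/(4 × 1.4)] / (ln 0.86)² = 348.2, so 349 intervention and 1396 controls, 1745 in total.

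The plan states 352, 1408 and 1760. The figure is reproduced within 1%, and power at 352/1408 is 80.4%. The sample size is not in dispute; it gives the scale for the bias.

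**2. Where patients can come from.**

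| Patient's clinician | Can be intervention? | Can be control? |
|---|---|---|
| Participating | Yes, if listed and consenting | Yes |
| Not participating | No | Not excluded by the text |

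The confounding is therefore partial at most, because controls also include patients of participating clinicians.

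**3. Illustrative size.** The documents give neither participation nor ED rates by clinician, so both inputs here are assumptions. Let q be the share of controls with non-participating clinicians and R the ED rate of those patients relative to patients of participating clinicians. With no true effect and no adjustment:

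apparent rate ratio = 1 / [(1 − q) + qR]

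| q | R | Apparent ratio | Two-sided rejection at 352/1408 |
|---|---|---|---|
| 0.2 | 1.2 | 1/1.04 = 0.962 | about 12% |
| 0.4 | 1.2 | 1/1.08 = 0.926 | about 32% |
| 0.4 | 1.4 | 1/1.16 = 0.862 | about 79% |
| 0.4 | 0.8 | 1/0.92 = 1.087 | not calculated |
| 0, or any q with R = 1 | | 1 | 5% |

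The rejection rates use a Poisson variance and a control rate of 1.4. For the second row, the intervention rate is 1.4/1.08 = 1.296, the standard error is √[1/(352 × 1.296) + 1/(1408 × 1.4)] = 0.052, and ln(1.08)/0.052 = 1.48, which exceeds 1.96 with probability about 0.32. Over-dispersion would widen the standard error and lower these rates, but would not change the apparent ratio.

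To imitate the whole target effect, q(R − 1) must equal 1/0.86 − 1 = 0.163, for example q = 0.4 with R of about 1.4. With R below 1, the bias hides benefit instead.

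**The case against.** A reader might infer that controls do include patients of non-participating clinicians, so that the comparison is confounded as a matter of fact. The documents do not go that far. The article speaks of potential controls, which leaves room for a later selection step in a fuller plan. All oncology staff are eligible and invited, and nothing says that any declined. If nearly all joined, the bias is close to zero. This stands, and the point must be conditional.

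The illustration is unadjusted and its inputs are assumed. What matters is the clinician difference left after adjustment. Specialty and tumour stream act largely through case mix, stage and treatment status are named covariates, the list is open-ended, and for participants cancer site and treatment details come from the oncology information system. Adjustment could remove part of the difference. This stands too; practice style would remain, which bears more on referrals than on ED visits.

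A reader might also conclude that the only sound primary controls are unenrolled patients of participating clinicians. That is debatable. Such a pool holds a higher share of people who declined and, unless screened, of people who fail the eligibility criteria. Participating staff receive training and refreshers, which may change how they refer all their patients. A broader pool dilutes both problems. The choice is a trade-off.

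None of this removes the difference between the stated sampling frames, and the article states no step that deals with it.

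**Conclusion.** The point holds as a possible, partial confounding. It rests on two things: the control section is limited by centre and not by clinician, and the named covariates are all patient-level. That some clinicians declined, and that their patients are among the controls, is inferred.

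Size and direction cannot be determined from the documents. Over the assumed range shown, the apparent null rate ratio runs from 0.86 to 1.09, so the bias could lie anywhere from imitating the full target to hiding more than half of it; it is zero with full participation or equal ED rates across practices. The referral outcome is the more exposed. The point merits a change to the extraction and analysis, not a redesign.

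**What to change.** **Control population:** extract, for every control, the treating clinician (participating or not), specialty, tumour site and centre, and hold the same fields for intervention patients.

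**Statistical analyses:** add specialty, tumour site and centre to the adjustment set for ED presentations and referrals. Pre-specify an analysis limited to controls who are patients of participating clinicians and who meet those eligibility criteria, listed under Patients, that the databases record. Report it beside the all-controls analysis.

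**Cost:** a few more fields in an extraction that is already planned, and two or three sentences. The restricted pool will be smaller, possibly below 1408, and will contain a higher share of patients who declined. Spill-over from trained clinicians would generally pull the restricted estimate toward no effect. A gap between the two analyses cannot by itself separate spill-over from clinician confounding, so the two estimates should be read as a range.

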##### In clinic

Eligible patients attending a cancer care clinic will be invited to participate by a member of the clinical trial team in the waiting area. The trial research member will explain the study in detail and provide patients with a study pack containing a letter of invitation, participant information and consent form, demographics survey and reply-paid envelope. Consenting patients will be asked to complete a consent form and their first PROMPT-Care assessment just prior to their appointment.

##### Mail-out

For patients who require additional time to consider participation, or those in follow-up who do not have regular clinic appointments, research staff will mail out a study pack inviting them to participate, then follow up by phone to answer any questions and provide additional information, as required.

#### Assessment completion

Patients will complete PROMPT-Care assessments on a monthly basis and will be followed up for a minimum of four months. Patients will have the option to complete assessments either at the hospital in clinic, their home or any public community location. Patients completing assessments in clinic will be provided with a tablet device in the waiting area just prior to their scheduled appointment. Patients who complete assessments from home or in community locations will receive an email containing the survey link three days before their assessment is due.

### Measures

#### Outcomes

The primary outcome is number of emergency department (ED) presentations observed during the study period. Details about ED presentation dates, reason for presentation and any resulting admissions will be extracted from the electronic medical record (EMR) (Table 1).

**Table 1 Tab1:** Primary and secondary outcome data collected

Data	Description of data	Source of data
Primary Outcomes		
Emergency Department (ED) presentations	• ED presentations (date, number of visits) • Length of stay • Reason for presentation	Extracted from electronic medical record (EMR)
Secondary Outcomes		
Time on chemotherapy	• Planned chemotherapy regimen • Actual regimen start and end date • Toxicities, changes to treatment delivery and reasons	Extracted from oncology information system (OIS)
Referral to allied health services	• Date of referral and allied health service type • Reason for referral eg. emotional distress, case management etc.	Extracted from EMR & OIS

The secondary outcomes are time receiving active chemotherapy and referrals to allied health services. Details of planned and actual chemotherapy regimens as well as any toxicities and changes to treatment delivery will be extracted from the OIS. Date, reason and number of referrals to allied health services will be tabulated and extracted from the medical record and OIS.

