**Methods:**

Groups eligible to participate in the intervention arm of this controlled trial are patients receiving cancer care (including follow-up). PROMPT-Care patients will complete monthly assessments (distress, symptoms, unmet needs) until voluntary withdrawal or death. In Version 1.0, the care team accessed patients’ clinical feedback reports in ‘real time’ to guide their care, and patients received links to support their self-management, tailored to their PRO responses. Version 2.0 was extended to include: i) an additional alert system notifying the care team of ongoing unresolved clinical issues, ii) patient self-management resources, and iii) an auto-populated Treatment Summary and Survivorship Care Plan (SCP). The control population will be patients extracted from hospital databases of the general cancer patient population who were seen at the participating cancer therapy centres during the study period, with a ratio of 1:4 of intervention to control patients.

A minimum sample size of 1760 (352 intervention and 1408 control) patients will detect a 14% reduction in the number of ED presentations (primary outcome) in the PROMPT-Care group compared with the control group. Intervention patients will provide feedback on system usability and value of the self-management materials; oncology staff will provide feedback on usefulness of PROMPT-Care reports, response to clinical alerts, impact on routine care, and usefulness of the SCPs; and GPs will provide feedback on the usefulness of the SCPs and attitudes towards shared-care models of survivorship care planning.

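### The primary outcome window and the controls' start date are not fixed, so comparable at-risk time in the two arms is not secured and the rate ratio is open to bias of unknown direction

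*Protocol article*

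**What the plan says.** - **Outcome** (Protocol article, Outcomes): "The primary outcome is number of emergency department (ED) presentations observed during the study period". No patient-level start or end is given. The dates of ED presentations are extracted from the electronic medical record.
- **Intervention entry** (Patient identification and consent): clinicians review clinic lists to "identify eligible patients who have appointments scheduled within the coming two (2) months". Patients are then approached in clinic or by mail. Staggered entry is an inference from this, but a firm one.
- **Intervention follow-up** (Assessment completion): patients "will be followed up for a minimum of four months". The Abstract has monthly assessments continuing "until voluntary withdrawal or death". Patient evaluation plans a survey after the ninth assessment, which at monthly spacing falls about eight months after the first.
- **Controls** (Control population): drawn from the "general cancer patient population who were seen at the participating cancer therapy centres during the study period". No index date, minimum follow-up or end date is given.
- **Sample size**: rests on an "assumed rate of ED presentations being 1.4 visits per patient during the study period", a 14% reduction, a 1:4 ratio, 80% power and a 5% significance level.
- **Statistical analyses**: Poisson or negative binomial regression compares rates of ED presentations, adjusted for covariates. Person-time and an offset are neither named nor excluded.

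**The concern.** A count has meaning only relative to the time over which it was collected. In the intervention arm that time can start at consent, which varies by patient, or at the start of the study, which includes time before the intervention. In the control arm no start is given at all. In a non-randomised comparison the moment a control's clock starts is part of the design, because it also fixes the phase of disease and treatment at which controls are observed.

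The word rate does not settle this. Under Sample size it means visits per patient over the study period, not visits per unit of person-time. The target effect is only 14%, so a modest mismatch in observed time could produce it or hide it.

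**Working it through.** **1. The plan's own figure.** Inputs from Sample size: control mean 1.4 (the arm is not named; taken as control), rate ratio 0.86, so intervention mean 1.4 × 0.86 = 1.204; ratio 1:4; power 80%; 5% taken as two-sided. With a Poisson count, a Wald test on the log rate ratio and equal exposure:

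n1 = (1.960 + 0.842)² × [1/1.204 + 1/(4 × 1.4)] / (ln 0.86)² = 348.2, so 349.

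The stated figure is 352. Power at 352/1408 is 80.4%. The stated size is thus reproduced to within 3% by a per-patient count with the same exposure in both arms. The arithmetic is not in error.

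**2. Intervention counted from consent, controls over the whole period, no offset.** Let f be mean intervention exposure as a fraction of control exposure. The documents give no study length or entry dates, so f is an assumption and a range is shown. The expected ratio is f × the true ratio. With no true effect,

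SE = √[1/(352 × 1.4 × f) + 1/(1408 × 1.4)], and the rejection probability is Φ(−1.96 − ln f/SE) + Φ(−1.96 + ln f/SE).

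| f | Apparent ratio, no true effect | False-positive probability |
|---|---|---|
| 1.00 | 1.00 | 5% |
| 0.95 | 0.95 | 17% |
| 0.90 | 0.90 | 52% |
| 0.86 | 0.86 | 80% |
| 0.75 | 0.75 | 99.9% |

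Check at f = 0.86: SE = 0.0535, ln f/SE = −2.82, Φ(−1.96 + 2.82) = 0.80.

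**3. Controls with the shorter exposure, no offset.** If control exposure is 86% of intervention exposure, a true 0.86 appears as 0.86/0.86 = 1.00.

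**4. Both arms counted over the whole period.** Assume entry uniform from month 0 to month T − 4, so that everyone has at least four months. Mean time after consent is (T + 4)/2. If the intervention acts only after consent, the 14% reduction is multiplied by that fraction of T. Power is at 352/1408 with control mean 1.4.

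| T (months, assumed) | Fraction after consent | Diluted reduction | Power |
|---|---|---|---|
| 12 | 8/12 = 0.667 | 9.3% | 46% |
| 18 | 11/18 = 0.611 | 8.6% | 40% |
| 24 | 14/24 = 0.583 | 8.2% | 37% |

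**5. What an offset does.** In simulations (500 Poisson trials each, T = 12, intervention entry as in step 4, controls observed for all 12 months), a log person-time offset gave a ratio of 1.00 under no effect and 0.86 under a true 0.86. The length-related bias goes. Power was 67% (66% by formula).

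If control windows shorten in the same way, power is Φ(|ln 0.86|/SE − 1.96) with SE = √{[1/(352 × 1.204) + 1/(1408 × 1.4)]/f}. At f = 0.667, SE = 0.0656, |ln 0.86|/SE = 2.30 and power is 63%. Both figures take 1.4 as the mean over the full assumed period. If 1.4 was meant as the mean over the time actually observed, the loss is smaller or absent.

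**The case against.** The strongest reply is that this is a condensed article. It plans to compare rates with models that ordinarily carry a person-time offset, nothing excludes one, and the offset and data cut are commonly left to an analysis plan. That stands as far as it goes: a missing offset would not be a finding. It does not dispose of the point, because an offset needs a time zero, and the stated control definition supplies none. The stated outcome, followed literally, also counts visits before consent.

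Stronger readings that a reader might infer, and that the documents do not support:

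- **Exposure differs between arms and the ratio is biased.** No control window is given, so neither a difference nor its direction can be shown.
- **An offset is impossible.** ED dates are extracted and controls come from hospital databases, so a start date can be derived. It has simply not been fixed.
- **Intervention follow-up ends informatively at withdrawal.** The Abstract says "PROMPT-Care patients will complete monthly assessments (distress, symptoms, unmet needs) until voluntary withdrawal or death". That ends the assessments. ED visits come from the medical record, and nothing says that counting them stops.
- **Controls carry immortal time.** A control can have ED visits before the attendance that qualified them; only death is ruled out. Intervention patients must likewise survive to consent, and no differential effect has been shown.

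It is also fair to say that the study lengths in the working are assumed, and that steps 2 and 4 rest on mutually exclusive readings of the window. They show sensitivity and do not measure a known bias.

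**Conclusion.** The concern holds in this form: the outcome is a count over a calendar period, intervention follow-up varies, and a control is anyone "who were seen at the participating cancer therapy centres during the study period". Comparable at-risk time is not secured, and the rate ratio is open to bias of unknown direction.

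The size depends on the reading adopted. Without an offset, a 5% shortfall in intervention exposure more than triples the false-positive rate, and a 14% shortfall reproduces the whole target effect. Counting everything in both arms reduces a true 14% effect to between 8.2% and 9.3% for assumed periods of 12 to 24 months. These figures assume Poisson counts, a constant visit rate and, in the dilution case, uniform entry with a four-month minimum.

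This should be settled before analysis, because it decides whether the primary comparison can be interpreted.

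**What to change.** - Define the at-risk window alike in both arms: from consent (intervention) or an assigned index date (control) to the earlier of death and a common data-cut date.
- Take each control's index date from a clinic attendance, with index dates distributed by hospital and calendar month like the intervention consents. The article describes a 1:4 ratio and no individual matching, and none is needed.
- Use log person-time as the offset in the Poisson or negative binomial model.
- State that ED visits in the medical record continue to be counted after a patient stops the assessments, where consent permits.
- Reword the primary outcome as ED presentations per unit of person-time from consent or index date.

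**Cost:** revised wording, one derived date per control and a rule for assigning it. The 1.4 visits must be re-expressed per unit of person-time and the power recalculated. It may fall below 80%; the 12-month illustration gives about 67% with controls observed throughout and about 63% with control windows shortened like the intervention arm's.

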#### Patient clinical and socio-demographic characteristics

Upon consenting, participants will complete a questionnaire about socio-demographics including: marital status, education level, employment status and language spoken at home. Additional demographics (eg. age, gender and need for interpreter) and clinical characteristics such as date of diagnosis, site (ICD-10), stage (TNM classification) and treatment details will be extracted from the OIS.

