### Study population

#### Patients

Eligible patients are people who are either currently receiving cancer care (including follow-up care) or have recently been diagnosed with cancer and are scheduled to commence cancer treatment at one of the four participating sites. Eligibility criteria include a confirmed diagnosis of cancer, age 18 years or over, cognitively able to provide informed consent and understand the surveys, and ability to complete the survey in English. Exclusion criteria are having a diagnosis of a blood cancer and not having access to the Internet outside of the clinic.

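### The only stated source for marital status, education, employment and home language is a consent questionnaire with no described counterpart for the database controls, so as written these four variables cannot enter the between-arm comparison

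*Protocol article*

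**What the plan says.** The protocol article assigns baseline variables to two sources in its section on patient clinical and socio-demographic characteristics.

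- **Questionnaire.** "Upon consenting, participants will complete a questionnaire about socio-demographics including: marital status, education level, employment status and language spoken at home". The In clinic section shows how it reaches patients: the study pack given to those invited contains the "participant information and consent form, demographics survey and reply-paid envelope". The Mail-out section sends a study pack to the other invitees.
- **Oncology information system (OIS).** "Additional demographics (eg. age, gender and need for interpreter") come from here, as do date of diagnosis, cancer site, stage and treatment details.

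The Control population section says that a list of potential controls "will be extracted from hospital databases of the general cancer patient population" seen at the participating centres during the study period. It describes no approach, consent or survey for them.

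Under Statistical analyses, "Descriptive statistics will be generated for all socio-demographic and clinical characteristics, and outcome measures". The ED model is a Poisson or negative binomial regression, "adjusting for covariates (such as age, sex, stage of disease, and treatment status").

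For intervention patients, the Patients section requires ability to complete the survey in English and adds: "Exclusion criteria are having a diagnosis of a blood cancer and not having access to the Internet outside of the clinic". The Control population section does not repeat these conditions.

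**The concern.** Without randomisation, the primary comparison depends on covariates measured in both arms. The intervention group is self-selected: its members agreed to take part, have Internet access outside the clinic, can complete the survey in English and accept monthly assessments. Education, employment and home language plausibly go with those traits, and social position plausibly goes with ED use.

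The four variables that would describe this difference have a stated source in the intervention arm only. If the extraction follows the article, nobody can see how far the arms differ on them, and the ED model cannot allow for them. Part of any fall in ED presentations could then reflect who volunteered, and a reader could not judge how much.

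**Working it through.** **1. Sources set side by side**

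| Variable | Stated source | Intervention | Controls |
|---|---|---|---|
| Marital status, education, employment, home language | Questionnaire on consenting | Yes | None described |
| Age, gender, need for interpreter | OIS | Yes | Obtainable |
| Site, stage, treatment details | OIS | Yes | Obtainable |

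Every covariate named for the ED model (age, sex, stage, treatment status) falls in the OIS rows, so the adjustment as listed can be carried out. None of the four questionnaire variables is named. A variable that is missing for every control cannot be used to adjust a comparison of the two arms.

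**2. The plan's own figure, as a benchmark**

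Inputs from the Sample size section: 1.4 visits per patient, a 14% reduction (rate ratio 0.86), 1:4 allocation, 80% power and 5% significance, taken here as two-sided. With a Poisson comparison on the log rate ratio:

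n(intervention) = (1.960 + 0.842)² × [1/(1.4 × 0.86) + 1/(4 × 1.4)] / (ln 0.86)² = 7.849 × 1.0091 / 0.02275 ≈ 349

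Controls: 4 × 349 = 1396. Total: 1745. The article states 352 + 1408 = 1760, at which the same formula gives 80.4% power. The sample size is reproduced closely and this point does not affect it. It serves only to fix 0.86 as the yardstick.

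**3. Illustration of size (all inputs assumed, none from the documents)**

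Take one binary social factor with prevalence p₁ in the intervention arm and p₀ in controls. Patients with the factor have g times the ED rate of those without. If the intervention does nothing, the unadjusted rate ratio is

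(1 − p₁ + p₁g) / (1 − p₀ + p₀g)

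- p₁ = 0.60, p₀ = 0.35, g = 0.75: (0.40 + 0.45)/(0.65 + 0.2625) = 0.850/0.9125 = 0.93
- p₁ = 0.50, p₀ = 0.40, g = 0.85: (0.50 + 0.425)/(0.60 + 0.34) = 0.925/0.940 = 0.98

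The answer depends on the inputs chosen. With p₀ = 0.40 throughout:

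- p₁ = 0.50, g = 0.9: 0.95/0.96 = 0.99
- p₁ = 0.70, g = 0.6: 0.72/0.84 = 0.86

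The last case equals the whole target effect and the one before it is negligible. All four calculations ignore the planned adjustment for age, sex, stage and treatment status, and all assume that the factor is commoner in the intervention arm and lowers ED use.

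**The case against.** The case against has several sound parts.

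- **The lists are open.** The OIS demographics are introduced by eg. and the covariates by such as. The hospital record may hold marital status or language, and need for interpreter already captures part of the language difference. A reader might infer that social differences between the arms can be neither shown nor adjusted for at all. The documents do not support that: the statement holds for the four named variables through their stated source, and no further.
- **No contact with controls is an inference.** The article never says outright that controls receive no questionnaire. The inference is reasonable from a database extraction with no approach described, but it is still an inference.
- **There is no contradiction in the analysis section.** A reader might take the promise of descriptive statistics on all socio-demographic characteristics as a promise of a two-column table. It is not worded that way, and describing the intervention arm alone would satisfy it.
- **No named analysis fails.** Every listed covariate has an OIS source.
- **An article condenses.** The full covariate list and extraction fields could sit in a fuller protocol or analysis plan.

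The last objection does not dispose of the point. The article does not merely omit a source: it states one, and that source serves one arm. An analysis plan can add covariates, but it cannot adjust for values that were never obtained in controls. The remedy belongs at data extraction.

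Whether controls should meet the same Internet and language conditions is a separate question, which measuring social variables would not settle.

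**Conclusion.** The point holds in a limited form. By the stated routes, marital status, education, employment and home language are available for the intervention arm only, and no social variable is named for adjustment in a comparison where one arm volunteered. This should be put right before the data are extracted.

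The size of any bias is unknown. The 0.93 to 0.98 range (an apparent reduction of about 7% to 2%) rests wholly on assumed prevalences and rate ratios and is unadjusted. It should not be read as an estimate of what the trial will show, nor as evidence that a 14% reduction would be spurious. Even the direction of the bias is assumed. What the illustration does show is that a moderate social imbalance could produce an apparent effect that is not trivial beside the target.

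**What to change.** For both arms, extract from the same hospital record source whichever social fields it holds: for example marital status, preferred language or need for interpreter, and residential postcode mapped to an area-level socioeconomic index. Tabulate them by arm, and add the area index and the other both-arm fields to the primary ED model. Use the questionnaire only to describe the intervention arm. Do not set its answers against record-based values for controls, because a difference in source would then be mixed with a difference between arms. State that individual education and employment remain uncontrolled.

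The cost is a few more fields in an extraction already planned and a sentence in the analysis section, with no contact with controls. The limits should be stated too. That the fields are held is an assumption, registration data may be incomplete, and an area index is a coarse stand-in for individual circumstances. The change reduces the gap without closing it.
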